**Figure 1 F1:**
[figure not shown]
Study diagrams showing the selection of comparators and formation of analysis cohorts for emulating a target trial of discontinuation of inhaled corticosteroids (ICS) using the UK Cystic Fibrosis Registry (UKCFR), using the prevalent new-user design. Dotted green lines represent time an individual is taking ICS but not yet eligible for inclusion in the base cohort, solid green lines represent time an individual is taking ICS after more than 3 months of initial use, dotted blue lines represent time an individual is no longer taking ICS. (a) Five example individuals who meet the eligibility criteria for inclusion in the base cohort, where 1–3 discontinue ICS in the study period. (b) The criteria for being in each of the discontinuer’s exposure sets in calendar time (6 months either side date of discontinuation). (c) Individuals 2 and 5 are included in individual 1’s exposure set due to similarity in both calendar time and ICS exposure history. (d) Only individual 5 would be included in individual 2’s exposure set and (e) only individual 4 would be included in individual 3’s exposure set.

**Figure 2 F2:**
[figure not shown]
Study diagram showing the selection of comparators and formation of analysis cohorts for emulating a target trial of discontinuation of inhaled corticosteroids using the UK Cystic Fibrosis Registry (UKCFR), using the prevalent new-user design (PNUD) on an alternative time scale (time since eligibility). This diagram displays five example individuals who meet eligibility criteria for inclusion in the base cohort (the same as in figure 1), with the exposure sets on a time since eligibility time scale (a PNUD visualisation commonly used to display the organisation of prevalent new-users and comparators in the analysis cohort).^17^

#### Sequential trials design

The sequential trials design is an alternative method which has elsewhere been referred to as the sequential trials approach, successive trials or sequential Cox approach.^20^,^22^ Under this design, a sequence of artificial ‘trials’ will commence at successive regularly spaced time points. At each time origin, the set of individuals meeting the eligibility criteria will be divided into ICS discontinuers and continuers based on treatment start and stop dates as recorded in the UKCFR, emulating a series of successive ‘trials’ from January 2016 to June 2018 (see figure 3). For example, this may entail successive monthly trials within which continuers and new discontinuers are identified. Eligible individuals who continue ICS may be included in multiple artificial trials. For example, individuals eligible for the trial commencing January 2016 but who do not discontinue ICS in that period will be eligible to be included in the next trial if they meet the eligibility criteria, and so on. Eligible individuals can appear as discontinuers in only one trial, but discontinuers may appear in earlier trials as continuers.

**Figure 3 F3:**
[figure not shown]
Study diagram showing the selection of comparators, artificial trials and formation of analysis cohorts for emulating a target trial of discontinuation of inhaled corticosteroids (ICS) using the UK Cystic Fibrosis Registry (UKCFR), using the sequential trials design on the calendar time scale. This diagram displays five example individuals (the same as in figures1  2) who meet eligibility criteria of a sequence of four artificial sequential trials in the study period. Within each artificial trial, individuals are separated into ICS discontinuers and continuers, with time zero being the date of discontinuation for discontinuers and the first calendar day of the trial for the continuers.

### Target trial emulation

#### Time periods

##### Prevalent new-user design

We specify a study eligibility period between 1 January 2016 and 30 June 2018 since exact medication start and stopping dates are available in the UKCFR from 2016 onwards. The end of the eligibility period is chosen to ensure the study follow-up ends before (1) highly effective CFTR modulator therapies became widely prescribed in the UK and (2) the SARS-CoV-2 pandemic affected care pathways and data collection.^23^ Individuals who meet the eligibility criteria within this period will form the base cohort. For comparison, participants were recruited between November 2001 and July 2004 in CF-WISE.^12^

##### Sequential trials design

The same study period between 1 January 2016 and 30 June 2018 is specified, organised into regularly spaced (eg, monthly) artificial trials within that time period. Individuals are eligible for the first trial if they meet all the eligibility criteria (see *Inclusion and exclusion criteria*) on 1 January 2016. This approach is then applied, with updated covariate data where available (at annual reviews), to every successive new time origin between January 2016 and June 2018.

### Time zero

#### Prevalent new-user design

Time zero in the analysis is equivalent to the time of randomisation in the target trial, defined here as the time at which individuals meet all the eligibility criteria and first discontinue ICS or meet the criteria for being a comparator within an exposure set, thereby entering the emulated trial (see figure 4). In this analysis, due to the availability of exact dates of starting and stopping treatment, ICS continuers are assigned the exact stopping date of the discontinuer as their time zero. This date acts as the time zero for each individual within the exposure set.

**Figure 4 F4:**
[figure not shown]
Flow charts for selection of eligible individuals for emulating a target trial of discontinuation of inhaled corticosteroids (ICS) using the UK Cystic Fibrosis Registry (UKCFR), using the prevalent new-user design (PNUD) and sequential trials design. (i) In the PNUD, the first step is formation of a base cohort. The analysis cohort is formed of ICS discontinuers and reweighted comparators who continue ICS. This diagram represents the specifications for the analysis cohort. (ii) In the sequential trials design, individuals enter successive artificial trials at regularly spaced time intervals from new time origins (eg, successive monthly trials with new time origins at the first calendar date of each month in the study period). The ‘trials’ consist of ICS discontinuers and continuers and are analysed as a pooled dataset. T_0_=time zero (date of ICS discontinuation). ~Have a valid annual review in the study period. *Aged ≥6 years, report a FEV_1_ ≥40% predicted (at most recent annual review), using ICS for more than 3 months, no intravenous antibiotics in the 4 weeks prior to time zero.

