## Methods and analysis

### Data source

The UK CF Registry (UKCFR) is a centralised national database sponsored and managed by the CF Trust, which collects real-world data from all specialist CF centres in the UK.^15^ It holds data on an estimated 99% of the UK CF population covering demographic and longitudinal clinical data and was highlighted by the UK National Institute for Health and Care Excellence real-world evidence framework as an exemplar data source for evidence generation.^16^

Data collection for the UKCFR began in 1996 and is primarily structured around annual review visits, taking place approximately 1 year apart. In addition, demographic data including sex, ethnicity, diagnosis data and genotype are collected at enrolment into the Registry and usually remain time-invariant. Information is captured annually on events or conditions that have happened since the previous annual review, including complications, infections, treatments and hospital admissions. Other information collected at the date of each annual review includes results from pulmonary function tests, weight and height. Extracts of data recorded at annual reviews are provided to researchers for approved projects. In 2016 variable domains were added, including exact start and stop dates of medications.

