### Study design

We will use UKCFR data to conduct an emulation of a target trial based on the CF-WISE trial. This will be done using two study designs: (1) the PNUD and (2) the sequential trials design.^3 17^ The two study designs use distinct but related approaches to making use of observational data and applying statistical analyses to estimate causal effects, with control for measured confounding and time-related biases being at both design and analysis phases.^3 17^ The data used for these emulations will be from 2016 to 2018, chosen intentionally based on data quality and completeness in the UKCFR data and being in the pre-CFTR modulators era. Table 1 specifies the protocol components of the index trial (CF-WISE), the corresponding target trial (hypothetical RCT we would undertake if it were feasible) and how each element of the target trial will be emulated using UKCFR data.

**Table 1 T1:** Specification and emulation of a target trial of deprescribing from inhaled corticosteroids in the UKCFR

Protocol component	CF-WISE (index randomised trial*)	Target trial	Target trial emulation using UKCFR
Eligibility criteria	People diagnosed with CF aged ≥6 years, with FEV _1_≥40% predicted, sustained ICS use ≥3 months. Recruitment period November 2001 and July 2004. Excluded are people who used oral corticosteroids, high-dose ICS or intravenous antibiotics in the 4 weeks prior to treatment assignment.	Same as CF-WISE, except study period is between January 2016 and June 2018. This period reflects a balance between data quality and completeness in UKCFR and prior to the widespread introduction of CFTR modulators.	Prevalent new-user design*:* Same as target trial, except ICS dosage was not recorded. Individuals are eligible for the base cohort (see *Study design*) on the earliest date within the study period that they meet all eligibility criteria. Sequential trials design: Same as target trial, except ICS dosage not recorded. Successive regularly spaced ‘trials’, with eligibility criteria redefined based on most recent data if available.

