Treatment strategies	Following a 2-month run-in period receiving fluticasone propionate, participants either: continue to take fluticasone, or switch to taking placebo.	Participants either: continue to take ICS (any ICS, not limited to fluticasone propionate) for the duration of follow-up, or discontinue ICS and remain not taking it for the duration of follow-up.	Prevalent new-user design: Same as target trial, with information on (dis)continuation obtained using prescription start and stop dates. Sequential trials design: Same as the PNUD.
Assignment procedures	Randomisation to treatment strategy Investigators and participants blinded to assignment.	Same as CF-WISE.	Prevalent new-user design: For each discontinuer, comparators will be selected into time-based exposure sets that correspond to each ICS discontinuer. Comparators within each exposure set will then be reweighted to resemble the discontinuers. Sequential trials design: Sequence of artificial ‘trials’, with discontinuers and continuers defined within each regularly spaced ‘trial’. Potential for re-use of continuers across multiple trials. Confounder adjustment is through regression. In the absence of randomisation, treatment assignment is assumed to be random conditional on ICS treatment history and the measured covariates specified in *Covariates*.
Follow-up and index date	Follow-up starts at randomisation and ends at loss to follow-up, meeting criteria for early trial withdrawal, or 6 months of follow-up, whichever occurs first.	Same as CF-WISE	Prevalent new-user design: Follow-up starts at date of ICS discontinuation for both the discontinuers and the reweighted continuers. Sequential trials design: Follow-up starts at the date of ICS discontinuation for the discontinuers and the date of the start of each successive ‘trial’ for the continuers in that trial. For the primary outcome, individuals will be followed up to first pulmonary exacerbation, death, transplant or 6 months after treatment assignment, whichever occurs first. For information on follow-up for secondary outcomes (lung function) see online supplemental material appendix 1.

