#### Covariates

In the emulated trials, treatment discontinuation or continuation is not randomised and so measured potential confounders of the relationship between ICS discontinuation and clinical outcomes must be adjusted for to meet the assumption of no unmeasured confounding, a requirement for unbiased causal effect estimation.^30^

Based on a priori clinical expertise, we will adjust for the following covariates at baseline: age, sex, genotype, body mass index z-score, CF-related diabetes, FEV_1_% predicted, home and hospital intravenous antibiotics, hospital admissions, *P. aeruginosa* infection, *Burkholderia* infection, non-tuberculous mycobacteria infection, allergic bronchopulmonary aspergillosis, pancreatic insufficiency, liver disease, inhaled bronchodilator use (captured as a separate variable to ICS), asthmatic status (as a proxy to atopic status specified in CF-WISE), inhaled antibiotic use and mucoactive therapy use (hypertonic saline, mannitol and DNase).

For both the PNUD and sequential trials design, these covariates will be recorded at the nearest annual review date preceding time zero. Since ICS stopping dates may occur at any point between successive annual reviews, stopping dates will occur at various time intervals following baseline annual review across individuals. Therefore, time from previous annual review (in months) to time zero for both the discontinuers and continuers will be adjusted for in the analyses.

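### Entry can hinge on an annual review held after time zero, and primary follow-up has no end point for people whose registry coverage stops

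*Protocol article*

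**What the plan says.** **Entry.** The caption of Figure 4 (Time zero) carries the only annual-review condition for inclusion: "Have a valid annual review in the study period". Under Time periods the article states: "We specify a study eligibility period between 1 January 2016 and 30 June 2018". The first sequential trial opens on the first day of that period: "Individuals are eligible for the first trial if they meet all the eligibility criteria" on 1 January 2016.

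**Baseline.** FEV1 is taken at the most recent annual review (Inclusion and exclusion criteria). For the confounders, "these covariates will be recorded at the nearest annual review date preceding time zero" (Covariates). Study design limits the data window: "The data used for these emulations will be from 2016 to 2018". Eligibility also looks back 4 weeks (Table 1 and Figure 4; 1 month under Inclusion and exclusion criteria) for intravenous antibiotics, and 3 months for ICS use.

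**Data capture.** The registry is "primarily structured around annual review visits, taking place approximately 1 year apart", and "Information is captured annually on events or conditions that have happened since the previous annual review" (Data source). Researchers receive extracts of what was recorded at those reviews.

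**Exit.** In Table 1, CF-WISE follow-up ends at loss to follow-up, early withdrawal or 6 months, and the target trial copies this. In the emulation, "individuals will be followed up to first pulmonary exacerbation, death, transplant or 6 months after treatment assignment, whichever occurs first". Under Main analysis, the prevalent new-user Cox model censors at death or transplant, and the per-protocol analyses of both designs add censoring only for departure from the assigned strategy.

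**The concern.** Both ends of follow-up depend on annual reviews, and neither rule allows for that.

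At entry, a condition that a later visit can satisfy selects people who lived and stayed in the registry long enough to attend it. Those who died or left beforehand drop out after time zero, which is the type of selection that target trial emulation is meant to prevent.

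At exit, intravenous courses reach the registry through the next review. A person with no later review has no recorded course. A follow-up list that does not end at loss of coverage then credits that person with 6 event-free months. This depresses the marginal cumulative incidence and distorts the contrast if coverage differs by arm.

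The benchmarking criteria make even a modest distortion matter. One asks whether the direction of the HR agrees with CF-WISE, whose estimate was 1.07 (0.68 to 1.70), close to 1.

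**Working it through.** The article gives no attendance rates, event rates or power figure, so there is no stated number to reproduce. The check is date logic plus illustrations on stated assumptions.

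**1. Share of time zeros that depend on a later review**

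Inputs: a 30-month period (Time periods) and reviews about 12 months apart (Data source). Assumed: review dates spread evenly over the year, and time zeros spread evenly over the period.

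- For a time zero *t* months into the period, the chance of no earlier in-period review is 1 − *t*/12 for *t* below 12, and 0 afterwards.
- Integrating over 0 to 12 gives 6 months, and 6/30 = 20%.
- With 30 monthly origins (*t* = 0 to 29) the sum is 12 − 66/12 = 6.5, and 6.5/30 = 21.7%. For 10- and 14-month spacing the corresponding shares are 5.5/30 = 18.3% and 7.5/30 = 25%.
- In the 1 January 2016 trial the share is 100%, barring a review that same day.
- Mean wait to the qualifying review: the integral of (1 − *t*/12)(12 − *t*)/2 is 24, and 24/6 = 4.0 months.

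Under 12-month spacing, the review preceding each of these time zeros falls in 2015.

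**2. Look-back**

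For a time zero in January 2016, all or part of the intravenous look-back lies in December 2015. Data checks and feasibility analysis describes these dates as reliable only from 2016. This affects about one month of 30, or 3%.

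**3. Coverage at the end of the window**

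Assumed: reviews are held only to 31 December 2018 (month 36, one reading of the stated data window), with perfect attendance. The last review is then uniform over months 24 to 36.

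- Full 6-month coverage is missing with probability (*t* − 18)/12 for *t* from 18 to 30. The integral is 6 months, and 6/30 = 20%.
- There is no coverage at all with probability (*t* − 24)/12 for *t* from 24 to 30. The integral is 1.5 months, and 1.5/30 = 5%.
- For January to June 2018 the averages are (27 − 18)/12 = 75% without full coverage and (27 − 24)/12 = 25% with none.

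**4. Effect of counting unobserved people as event-free**

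Assumed: true HR 1, 6-month risk *r*, and a share *u* of an arm with no later review. Observed risk = *r*(1 − *u*). HR ≈ ln(1 − risk in discontinuers)/ln(1 − risk in continuers).

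| Unobserved | *r* = 0.20 | *r* = 0.35 | *r* = 0.50 |
|---|---|---|---|
| 10% of continuers only | HR 1.12, RD +2.0 points | HR 1.14, RD +3.5 | HR 1.16, RD +5.0 |
| 10% of discontinuers only | HR 0.89, RD −2.0 | HR 0.88, RD −3.5 | HR 0.86, RD −5.0 |
| 5% of both | HR 1.00, risks 0.19 | HR 1.00, risks 0.33 | HR 1.00, risks 0.475 |

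Worked example for the first cell: ln(0.80)/ln(0.82) = 1.12.

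**The case against.** **Entry.** Figure 4 is not shown, so the box to which the footnote belongs cannot be seen; it may only describe the registry source population. Criteria are applied at time zero, and FEV1 and covariates come from earlier reviews. A reader might infer that future clinical values decide eligibility. The text does not support that: only the registry-review condition lacks a date relative to time zero. The point is selection on a future visit.

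A reader might also apply 20% to the 536 discontinuers found at feasibility and call the resulting 107 people the bias. They are people who could qualify through a later review, and most would be included under either rule. Bias comes from those who died or left first, whose number is unknown. The 536 is also a count before the other exclusions.

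**Data window.** The rule that baseline precedes time zero already implies 2015 reviews, and the registry dates from 1996. The two passages therefore need reconciling, but nothing prevents use of the data. The article does not show that the ICS look-back is unavailable: date fields were added in 2016, but dates entered in them may be earlier.

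**Exit.** No sentence says that unobserved people are carried forward event-free, and the supplementary appendix or a full plan could add censoring. The registry covers an estimated 99% of the UK CF population, and intravenous dates are described as reliable. Reviews from 2019 may be held, since the lung-function outcome uses the next review at least 3 months after time zero. Anyone who enters through a later review does have some later coverage. These points reduce the likely size. They do not remove the problem, because the primary list is closed, it drops an end point that the target trial has, and reliable dates say nothing about people with no later review.

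**Direction.** It is tempting to assume that discontinuers attend less, so that stopping looks safer. The reverse is also plausible: if stop dates are entered at the next review, every identified discontinuer has a later review and a continuer need not.

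**Conclusion.** The point holds for the two rules as written. The entry condition can be met after time zero for about 20% of time zeros (18% to 25% over monthly origins with 10- to 14-month spacing), all within roughly the first year of the period. The primary follow-up list, unlike the target trial's, has no end point for loss of coverage. The stated data window and the January 2016 intravenous look-back also need aligning with the baseline rule.

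Counting uncovered time as event-free lowers both cumulative incidences. It moves the HR and risk difference if coverage differs by arm. At 10% in one arm only, the HR distortion is about 12% to 16% upward or 11% to 14% downward. The sign is undetermined, and all percentages rest on assumed review timing, coverage and risk. The article supports neither a claim that the bias favours discontinuation nor an estimate of its actual size. This should be corrected before analysis; it does not undermine the design.

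**What to change.** - **Figure 4:** require the valid annual review to fall on or before time zero.
- **Study design:** state that reviews before 2016 supply baseline data.
- **Time periods:** begin time zeros once the intravenous look-back is covered by dated records, and the ICS look-back too if earlier start dates are not held.
- **Table 1, primary follow-up:** add 'or the last date covered by a subsequent annual review'. Censor there, and include that censoring in the inverse probability of censoring weights. The article describes such weights only for the per-protocol analysis, so the intention-to-treat analysis would need them as well.
- **Check first:** establish whether stop dates are entered only at the following review. If so, discontinuers are selected on a later visit whatever Figure 4 says, and this should be reported as a limitation.

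Cost: wording changes, an extract of earlier reviews and one more censoring model. Covering the intravenous look-back removes about 1/30 (3%) of time zeros. Covering the ICS look-back, only if it proves necessary, means an April 2016 start and removes about 3/30 (10%). Both shares assume time zeros evenly spread over the period.

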#### Sequential trials design

In each trial in the sequential trials design, the time zero will be the stopping date for the ICS discontinuers, and the first day of the calendar time period for that trial for the comparators (those who meet the eligibility criteria and continue on ICS).

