#### Sequential trials design

The same inclusion and exclusion will be applied in the sequential trials design, except eligibility will be reassessed based on new information (if an annual review encounter takes place) between each successive trial. The criteria are applied at time zero for each trial, where the index date differs between discontinuers and continuers, unlike in the PNUD.

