#### Treatment strategies

The treatment strategies for the TTEs differ from the target trial due to lack of a placebo control. Instead, these analyses consider ICS discontinuation based on prescription data as the ‘treatment’ of interest and continued ICS use as the comparator treatment strategy. Whereas the index trial investigates discontinuation of fluticasone propionate only, the target trial and emulated trials are more pragmatic and will include all types of ICS (including in combination with bronchodilators). This reflects the heterogeneity of specific ICS or IC combination treatments documented within the UKCFR.

Discontinuation will be conceptualised as a point treatment strategy (ie, non-time-varying), where treatment status is determined at a single time point (time zero) for both ICS discontinuers and continuers.

These analyses will first estimate the observational analogue of an intention-to-treat (ITT) effect, which is the effect of being assigned to a treatment status.^24^ We will also target a per-protocol (PP) effect, which is the effect of adhering to the assigned treatment strategies. If in the real world individuals deviate from their assigned treatment (ie, discontinuers switch back to being on ICS and vice versa), the ITT and PP estimands differ and the ITT may be less relevant. See *Main analysis* for details.

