### Sensitivity analyses

Sensitivity analyses are planned to be the same in both the PNUD and sequential trials design. We will consider undertaking quantitative bias analysis (QBA) to quantify the potential impact of unmeasured confounding. QBA is an important set of tools for sensitivity analyses that test assumptions and impact of potential biases. One such technique is to use the strength of association between a confounder and outcome among unexposed, the strength of association between the confounder and treatment in the source population and the prevalence of the confounder as bias parameters.^39^

Robustness of results to the definition of the outcome will be assessed using an alternative definition for pulmonary exacerbation, restricting to hospital intravenous antibiotic use (excluding home use) and separately excluding intravenous episodes recorded as ‘planned’.

To address the potential for misclassification or failure to obtain accurate start and stop dates in the UKCFR, we will consider an alternative approach to the study design where an annualised definition of ICS discontinuation collected at annual review (whether the participant has stopped ICS since previous annual review) will be used.

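### Sequential trials design: continuers are followed from day 1 of each interval but identified by not stopping later in it, so their status is not fixed at time zero

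*Protocol article*

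**What the plan says.** **Time zero.** The Time zero section for this design says that "the time zero will be the stopping date for the ICS discontinuers, and the first day of the calendar time period for that trial"; the latter date applies to continuers. Table 1 (Follow-up and index date) and the Figure 3 legend say the same.

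**Forming the arms.** Under Study design, Sequential trials design, "this may entail successive monthly trials within which continuers and new discontinuers are identified". The worked example there says that "individuals eligible for the trial commencing January 2016 but who do not discontinue ICS in that period will be eligible to be included"; this refers to entry to the following trial. Arms are thus told apart over the whole period. The interval length is not fixed; monthly is offered as an example.

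**When status is set.** Treatment strategies, which applies to both designs, says that "treatment status is determined at a single time point (time zero) for both ICS discontinuers and continuers".

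**Eligibility.** Inclusion and exclusion criteria, Sequential trials design, applies the criteria at time zero, "where the index date differs between discontinuers and continuers, unlike in the PNUD".

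**The other design.** In the prevalent new-user design (PNUD), "ICS continuers are assigned the exact stopping date of the discontinuer as their time zero".

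**Annualised sensitivity analysis.** Sensitivity analyses says the authors will consider a version in which "an annualised definition of ICS discontinuation collected at annual review (whether the participant has stopped ICS since previous annual review) will be used". No time zero is given for it.

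**The concern.** Someone taking ICS on day 1 who stops on day 20 is on treatment at the continuers' time zero, yet is not counted as a continuer. Membership of the continuer arm is settled by what happens after its follow-up has started. If an exacerbation changes the chance of stopping in the rest of the interval, the continuer arm loses (or keeps) early events selectively.

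The discontinuers' own time zero is properly aligned. The fault lies in the continuer arm and in the comparison between arms.

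What is at stake is mainly the comparison of the two designs, which is a stated objective. The PNUD does not have this feature: both arms share one date, and in the Figure 1 legend individual 2, who stops later, still serves as a comparator for individual 1. An artefact in one design only would be mixed into any difference credited to estimand or method. The strengths box also says that both designs mitigate selection bias and immortal time bias.

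**Working it through.** **1. The passages side by side.** Take an intravenous course on day 5 and an ICS stop on day 20 of a monthly trial.
- Washout applied at the person's own time zero (Inclusion and exclusion criteria; Figure 4 legend, four weeks): the person fails it on day 20 and is not a continuer either. The day-5 event is in neither arm of that trial.
- Eligibility applied at the interval's origin (Time periods, first trial on 1 January 2016): the person is a discontinuer followed from day 20, and the day-5 event is still not counted among continuers.
- Status fixed at time zero (Treatment strategies): the person is a continuer on day 1 and the event counts.

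The same event in someone who stays on ICS counts on every reading. The sections cannot all hold.

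**2. Size.** The article gives no figure to reproduce, so this is an illustration with no true effect of stopping.

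From the article: 536 discontinuers before the other exclusions; 30 months; 6 months of follow-up. Stops per month = 536/30 = 17.9.

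Assumed: 1,000 to 2,200 eligible users at any time, so a monthly stopping share of 17.9/2,200 = 0.8% to 17.9/1,000 = 1.8%; 6-month exacerbation risk of 20% or 40%; discontinuers 2% of pooled records; stopping hazard multiplied by θ from the event to the end of the interval, with θ = 0, 1, 5 or 10.

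Formulas, in months, with interval length L:
- event hazard λ = −ln(1 − risk)/6; stopping hazard μ = −ln(1 − share)
- chance of being kept as a continuer after an event at t: exp(−μt − θμ(L − t)) if t < L, and exp(−μL) if t ≥ L
- continuer event density: λ·exp(−λt) times that chance, rescaled; discontinuer density: λ·exp(−λt)
- the HR solves the Cox score equation over 6 months

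| Risk, share | L | θ = 0 | θ = 1 | θ = 5 | θ = 10 |
|---|---|---|---|---|---|
| 20%, 0.8% | 1 | 0.9993 | 1.0000 | 1.0029 | 1.0064 |
| 20%, 1.8% | 1 | 0.9983 | 1.0000 | 1.0065 | 1.0142 |
| 40%, 0.8% | 1 | 0.9991 | 1.0000 | 1.0032 | 1.0071 |
| 40%, 1.8% | 1 | 0.9981 | 1.0000 | 1.0071 | 1.0158 |
| 20%, 0.8% | 3 | 0.9937 | 1.0000 | 1.0248 | 1.0554 |
| 20%, 1.8% | 3 | 0.9858 | 1.0000 | 1.0557 | 1.1229 |
| 40%, 0.8% | 3 | 0.9935 | 1.0000 | 1.0259 | 1.0582 |
| 40%, 1.8% | 3 | 0.9852 | 1.0000 | 1.0584 | 1.1302 |

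With status and start on one common date, the HR in this model is 1.00.

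**3. A second check.** A day-level simulation (15,000 people, 900 days, 0.7% stopping per month, stopping hazard 3 or 6 times higher for only 30 days after an intravenous start) gave continuer event rates of 0.998/0.997 of the correct value for 30-day intervals and 0.993/0.982 for 90-day intervals. These are smaller because the raised hazard does not last to the end of the interval.

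**4. Against the precision available.** Discontinuer events: 536 × 0.20 = 107 to 536 × 0.40 = 214. Their part alone of SE(log HR) is 1/√107 = 0.097 to 1/√214 = 0.068. The largest monthly distortion is ln(1.0158) = 0.0157, and 0.0157/0.068 = 0.23 SE. The largest quarterly one is ln(1.1302) = 0.122, and 0.122/0.068 = 1.8 SE. The true SE is larger, so these ratios are upper limits.

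**The case against.** **It is immaterial at the only interval named.** Quarterly or annual trials appear nowhere, and the benchmark CI from CF-WISE is 0.68 to 1.70. This stands for monthly trials. It does not remove the contradiction, and nothing in the text holds the interval at a month.

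**The events are not deleted from the analysis.** A reader might infer that they are. But discontinuers may appear as continuers in earlier trials, so with 6 months of follow-up the day-5 event can still count in overlapping earlier ones. This stands: the loss is from that one trial. The figures above already allow for it, since events at or after L are kept without selection.

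**The example sentence governs entry to the next trial.** True; it is not a definition of the current continuer arm. But the same section divides people into discontinuers and continuers within each period, and the Figure 3 legend agrees, so the look-ahead is the natural reading.

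**The bias need not run towards harm from stopping.** That inference is tempting, but it requires exacerbations to prompt stopping, and the article has no figure on this. With θ = 0 the HR falls below 1.

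**The annualised analysis does not repeat the problem on a 12-month scale.** A reader might infer that it does. The article only says it will be considered and gives no time zero. Starting at the earlier review would involve up to about a year of look-ahead (0.87 to 3.7 in the model above with L = 12). Starting at the review that reports the stop has no look-ahead, but begins follow-up up to about a year late. The documents choose neither.

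**A common date makes the design more like the PNUD.** Partly so. Use of all continuers, regression adjustment and the ability to target an ATE would still set it apart.

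**Conclusion.** The point holds as a contradiction in the text and an avoidable design fault in one of the two designs being compared. Continuer status uses information from after time zero, against the article's own rule, and the two arms have eligibility and washout checked on different dates.

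Under the assumed inputs the effect on a null HR is small for monthly trials (about 0.998 to 1.016) and larger for quarterly ones (about 0.985 to 1.13). It is nil if stopping is unrelated to events after day 1. The sign is not known. The size rests on assumed user numbers, risks and stopping behaviour, none of which the article supplies. The documents do not support saying that the planned analysis is biased towards harm or that the annualised analysis is invalid.

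**What to change.** - Set the interval at monthly or shorter.
- Within each interval, decide continuer status, eligibility and washout on a date common to both arms: for example a date drawn from that interval's discontinuer stop dates, or daily trials.
- Do not require continuers to stay on ICS for the rest of the interval. Treat later stopping as deviation, which the per-protocol analysis already handles by censoring and weighting.
- Reconcile the sequential-design text under Study design, Time zero, and Inclusion and exclusion criteria with Treatment strategies.
- If the annualised analysis is run, give it a time zero that does not classify people by stopping after follow-up starts, and acknowledge the delay between the stop and the start of follow-up. Date-based checks, such as shifting recorded stop dates, can be added but need not replace it: they cannot find unrecorded stops, a concern the Limitations section raises and the annual item might meet.

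**Cost.** Exact ICS and intravenous dates are already recorded, so this is data preparation. The common date need not remove any discontinuer. Drawn dates need a fixed seed. Daily trials mean 366 + 365 + 181 = 912 origins instead of 30, which lengthens the bootstrap.
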